### Randomization

The main analysis will be the comparison between patients assigned to EMDR vs those not assigned to EMDR. The secondary analysis, only amongst patients assigned to EMDR, will be the comparison between patients assigned to active-MtCS vs patients assigned to sham-MtCS. Therefore, the individuals will not randomly be assigned to one of the three arms. Instead, the patients meeting the inclusion criteria will be randomized twice: first to EMDR vs non-EMDR, and then those in the EMDR group to active-MtCS or sham-MtCS. For the sake of brevity, only the randomization to EMDR vs non-EMDR is described here, because the randomization to active-MtCS vs. sham-MtCS is identical. The variables used for the randomization will be age, educational level, and pain intensity score. The first two patients will be randomly allocated to EMDR with *p* = 2/3. For each subsequent patient, the following biased coin algorithm will be applied: if a group includes at least two more patients than it would have to have to maintain the ratio 2 EMDR / 1 control, the patient will be randomly assigned to the other group with *p* = 0.6. Otherwise, there will be a simulation of the new patient as it was allocated to EMDR and calculate the between-group standardized difference in pain intensity variable, then simulate that the new patient is allocated to non-EMDR and recalculate the difference, and finally randomly allocate the patient to the group associated to the smallest difference with *p* = 0.6. This strategy decreases prognostic imbalances between groups because it decreases differences in potential co-founders, yet still includes randomization.

Once the randomization group has been obtained, the principal investigator (PI) of the study will inform the participants accordingly. If the participants have been assigned to the EMDR group, the coordinator will also contact the therapist responsible of the treatment.

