There is increasing evidence which shows that, in addition to psychotherapeutic and pharmacologic interventions, tDCS is useful in treating FM and CP in terms of inducing pain relief and improving quality of life [32–46]. Interestingly, tDCS can also increase the therapeutic potential of other therapies when used in conjunction with them [47]. In this regard, a recent review has shown that the combination of tDCS with cognitive therapies, such as cognitive control therapy (CCT), increases its benefits when used for treating depressive disorders [47].

Taking into account the information presented above, we hypothesize that the combination of a trauma-focused therapy, such as EMDR, combined with tDCS targeted in the left dorsolateral prefrontal cortex (lDLPFC), could be a useful therapeutic option [48] for the treatment of patients with FM. The main reasons for selecting the lDLPFC are: (1) this region is critical in the regulation of the limbic system, implicated in emotion, which is hyperactivated in traumatized patients [49]; (2) it has been seen to be relatively hypoactivated in patients with depression [49–51], anxiety disorders [50, 51], and PTSD [52]; (3) there is a proved efficacy of lDLPFC tDCS in the treatment of resistant and non-resistant depression [47, 52], which suggests that FM patients will also benefit due to their comorbidities; (4) the lDLPFC also plays a central role in executive functions [53], and tDCS has the potential to improve cognitive functions associated with cortical plasticity, such as therapy-related learning processing [54].

Although in two studies it was found that the application of tDCS on the lDLPFC was generally less effective in reducing pain in FM patients compared to the application of stimulation on the primary motor cortex [35, 41], other studies were able to demonstrate a short-term efficacy in terms of pain and life quality [43], pain and fatigue [46], and pain and improvement in executive attention and orientation [42]. In all the studies mentioned, the stimulation applied over lDLPFC was anodal.

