## Methods/design

### Aims

The main objective of the study is to analyze whether EMDR therapy is effective in the reduction of pain symptoms in FM patients, and if its potential is boosted with the addition of MtCS. As secondary objectives, the study will analyze whether EMDR therapy is effective in reducing psychological trauma symptoms and comorbid symptoms of anxiety and depression, and in improving sleep quality and patient wellbeing, and if these effects are boosted by the addition of MtCS.

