### Study design

Within a double-blind randomized controlled design, patients will be randomized to (1) Waitlist Condition, (2) EMDR + active-MtCS (20 sessions), or (3) EMDR + sham-MtCS (20 sessions). All subjects will continue to receive their treatment as usual (TAU), regardless of the group to which they have been assigned during the study. If a participant does not attend 3 sessions consecutively, she will be withdrawn from the study. Psychotherapists and patients will be kept blind for MtCS treatment conditions until the end of the trial, and raters will be kept blind to both EMDR and MtCS conditions. It is not possible for patients to be blind to the EMDR condition due to its use of bilateral stimulation. The experimental condition assigned to the participants will only be revealed if the patient abandons the study. Otherwise, the blind condition will be maintained until the end of the study. All patients will be clinically evaluated at baseline, at post-treatment, and at 6 months from post-treatment as follow-up.

Figure 1 shows a flow chart of the progress of the study.

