### Data analysis

The distribution of the sociodemographic and clinical variables between groups at baseline will be summarized by descriptive statistics. We will use *t*-tests to compare pain levels at post-treatment and follow-up between groups (Waitlist vs EMDR; active-MtCS vs sham-MtCS). In order to avoid regression toward the mean and confusion effects, baseline levels of pain will be added as covariates, as well as age, depression and anxiety severity and number of years of education. Due to the sample size, no further analysis is expected. The statistical software used for the analysis will be R. For the principal statistical analysis, an intention to treat (ITT) analysis will be used, and multiple imputation for losses at follow-up. The dataset analyses during the current study will be available from the corresponding author on reasonable request.

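### The main test pools active-MtCS and sham-MtCS patients against an MtCS-free waitlist, so it estimates a package effect, while the Aims and Discussion read it as the effect of EMDR

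*Protocol article*

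**What the plan says.** The Aims section gives the target: "The main objective of the study is to analyze whether EMDR therapy is effective in the reduction of pain symptoms in FM patients". It then asks, as a separate question, whether MtCS boosts that effect. The Discussion, in the abstract and in the main text, promises an answer in the same terms.

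Under Study design, "patients will be randomized to (1) Waitlist Condition, (2) EMDR + active-MtCS (20 sessions), or (3) EMDR + sham-MtCS (20 sessions". There is no arm with EMDR alone and none with MtCS alone. The Waitlist condition section gives controls their usual treatment and nothing else, so they have neither active nor sham stimulation.

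The main comparison, in Randomization, is "The main analysis will be the comparison between patients assigned to EMDR vs those not assigned to EMDR". The second is: "The secondary analysis, only amongst patients assigned to EMDR, will be the comparison between patients assigned to active-MtCS vs patients assigned to sham-MtCS". The Data analysis section repeats these two, "between groups (Waitlist vs EMDR; active-MtCS vs sham-MtCS", and closes the list: "Due to the sample size, no further analysis is expected". No comparison of EMDR + sham-MtCS with the waitlist is planned, and the main comparison has no MtCS term. The Limitations section does not mention the pooling.

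**The concern.** The first conclusion (EMDR reduces pain) rests on a group in which some patients also receive an active intervention that the trial itself expects to help. If that expectation is right, the main estimate is too large as a measure of EMDR, and the more successful MtCS is, the larger the excess. A main result could be significant with no EMDR effect at all.

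The pooled contrast is not a factorial margin. In a 2×2 design the MtCS effect would be balanced across the EMDR and non-EMDR groups and would cancel. Here the non-EMDR group has no active-MtCS cell, so it does not cancel.

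**Working it through.** **Inputs.** From Sample size calculation: two-sided t-test, alpha 0.05, power 80%, d = 1, 13 and 26 evaluable, 15 + 30 randomized, 15% dropout. From Randomization: 2 EMDR to 1 control. Assumed: 1:1 active/sham split (13 + 13 evaluable), SD 1 in each arm, no covariate adjustment. Covariates would change power but not what is estimated.

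**The plan's own figure.** By the noncentral t, 12 + 24 gives 78.5% power at d = 1 and 13 + 26 gives 81.8%, so 13 + 26 reproduces. Dropout: 13 × 1.15 = 14.95 and 26 × 1.15 = 29.9, giving 15 + 30. The problem lies in the contrast, not in this arithmetic.

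**What the main contrast estimates.** Relative to the waitlist, the expected effect is e in the sham arm and e + m in the active arm. Pooled 1:1, this is (e + e + m)/2 = e + m/2.

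**How the planned test behaves when e = 0.** The standard error of the difference is √(1/13 + 1/26) = 0.340, and the critical t on 37 df is 2.026. The pooled group mixes two means, which inflates the variance the two-group t-test uses: its expectation is 1 + 26(m²/4)/37. At m = 1 this is 1.176 (SD 1.084). The shift is 0.5/0.340 = 1.47 standard errors and the threshold is 2.026 × 1.084 = 2.197, so the chance of significance is roughly 1 − Φ(2.197 − 1.472) = 1 − Φ(0.725) = 23%. Simulation of the planned test (at least 100,000 trials per scenario) gives 24 to 25%.

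| m (SD), with e = 0 | Pooled shift m/2 | Main test significant: planned two-group t-test | Same contrast in a three-group model | Power of active v sham (13 v 13) |
|---|---|---|---|---|
| 0.5 | 0.25 | 10% | 11% | 23% |
| 0.8 | 0.40 | 18% | 21% | 50% |
| 1.0 | 0.50 | 25% | 30% | 69% |

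The last column is the noncentral t on 24 df with noncentrality m/√(2/13). EMDR + sham v waitlist stays at 5% throughout, as it should when e = 0.

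**With a real but smaller EMDR effect.** At e = 0.5 and m = 1.0 the pooled shift is 0.5 + 0.5 = 1.0. The planned test is significant in about 77% of trials, although EMDR + sham delivers only half the design effect.

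**Does active v sham reveal the problem?** With e = 0, about 8% of trials at m = 0.5, and again at m = 1.0, combine a main result in favour of EMDR with a non-significant active v sham result. That pair would be read as EMDR working and MtCS adding nothing, the reverse of the truth in that scenario.

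**Adding the missing contrast.** EMDR + sham v waitlist at 13 v 13 has 68.7% power at d = 1. The effect detectable with 80% power rises from d = 0.98 (13 v 26) to d = 1.15.

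**The case against.** *The two planned contrasts already identify e.* This is the strongest reply, and it is right as far as it goes. With a 1:1 split and unadjusted means, pooled minus half of active v sham is (A + S)/2 − W − (A − S)/2 = S − W, which is the sham v waitlist difference. A reader might infer that a positive main result cannot be attributed to EMDR at all; the document does not support that, because m is estimated, though imprecisely. What stands against the plan is that it never takes this step, attaches no uncertainty to it, and rests the EMDR conclusion on the pooled test.

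*Stimulation may add little.* A reader might take the Background to say that this stimulation relieves fibromyalgia pain by itself. The sentence "tDCS is useful in treating FM and CP in terms of inducing pain relief and improving quality of life" concerns tDCS in general. The same section reports two studies in which stimulation of the trial's target area was generally less effective for pain than motor cortex stimulation, and says that MtCS of that area is unexplored. So m > 0 is the trial's hypothesis, not an established fact, and the values of m used here are illustrative. The case e = 0 with large m is a stress test, not a forecast.

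*Larger error rates could be quoted.* Treating the pooled group as having SD 1 gives 30%, 21% and 11% (and 82% at e = 0.5, m = 1.0). Those belong to a three-group model. The planned two-group test carries the extra spread, so 25%, 18%, 10% and 77% apply.

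*The split is not stated.* True: the second randomization is only called identical to the first. Read literally as 2:1 in favour of active, the share would be 2m/3 rather than m/2, so the problem would be larger.

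*Lack of blinding and a waitlist comparator are open choices.* Also true: "It is not possible for patients to be blind to the EMDR condition due to its use of bilateral stimulation" is stated plainly, and double-blinding is described for the MtCS condition. This is no hidden flaw and is not the point here.

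*The trial is exploratory and pragmatic.* That can justify testing a package, but the conclusion should then name the package.

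**Conclusion.** The point holds as a mismatch between the stated conclusion and the planned main contrast. The contrast estimates e + m/2 under a 1:1 split and equals the EMDR + sham effect only if the second hypothesis is false. For e = 0 and m between 0.5 and 1.0 SD, the main test is significant in about 10% to 25% of trials, two to five times the nominal 5%. These figures assume 13/13/13 evaluable, a common SD and no adjustment; the direction depends only on m > 0.

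The pooled test remains a valid test of EMDR with active or sham MtCS against usual treatment, and its sample size is sound for that purpose. Because the article lists its contrasts and expects no others, this is not simply a detail left to an unseen analysis plan. It should be settled before the trial restarts.

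**What to change.** 1. Fit one three-group linear model (waitlist, EMDR + sham, EMDR + active) with the covariates already planned.
2. Keep the pooled contrast, reported as the effect of EMDR with active or sham MtCS against waitlist.
3. Pre-specify EMDR + sham-MtCS v waitlist, and rest any statement about EMDR without active stimulation on it. Say that this contrast still includes sham-device contact and the expectation of patients who know they receive EMDR.
4. Keep active v sham as the secondary contrast, and state the intended active/sham ratio.
5. State the order of testing so that type I error is controlled; for example, test sham v waitlist only if the pooled test is significant, and say whether active v sham falls inside or outside that sequence.
6. Align the wording of the Aims and Discussion.

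**Cost.** No new arms, visits or patients are needed, and since the Trial status section plans to restart from the beginning, the change can precede enrolment. The price is power: about 69% at d = 1 for sham v waitlist (13 v 13), against 82% for the pooled contrast when m = 0. The protocol should say so. If 80% were wanted for the added contrast at d = 1, it would take 17 evaluable per arm, or 17/0.85 = 20 randomized per arm and 3 × 20 = 60 in all. That is an option, not a condition of the fix.

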### Sample size calculation

The main tests of the study will consist of assessing whether patients assigned to EMDR show different levels in the pain intensity variable using a standard formula for two-tailed *t*-tests. The total sample size required to detect large to very large effect size differences (Cohen’s *d* ≥ 1) between two groups with a significance level of 0.05 and statistical power of 80% is 13 and 26. Assuming 15% dropouts, we will aim to randomize 45 patients, i.e., 15 + 30, so that after removing ~ 15% dropouts we would have approximately 13 + 26.

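### Two separate two-group models are valid but give up some power: up to about 5 points in each comparison if MtCS has a 1 SD effect, and little or none if it does not

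*Protocol article*

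**What the plan says.** The Randomization section of the protocol article fixes two comparisons. The first: "The main analysis will be the comparison between patients assigned to EMDR vs those not assigned to EMDR". The second: "The secondary analysis, only amongst patients assigned to EMDR, will be the comparison between patients assigned to active-MtCS vs patients assigned to sham-MtCS". It gives a design reason, namely that patients are randomised in two stages, with one comparison per stage.

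The Data analysis section carries this out as two two-group tests at post-treatment and at follow-up. It states that "baseline levels of pain will be added as covariates, as well as age, depression and anxiety severity and number of years of education", and it plans no analysis beyond these because of the sample size. Counting depression and anxiety separately, that is five covariates. No model holding all three arms is described.

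The Sample size calculation section plans only the EMDR comparison, for "large to very large effect size differences (Cohen’s *d* ≥ 1) between two groups". It arrives at 13 and 26 evaluable patients. No effect size is given for MtCS anywhere in the article.

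**The concern.** There are two sources of lost precision.

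- **EMDR vs waitlist.** Active and sham are treated as one group. Any true difference between them stays in the residual, although the assigned arm would explain it. The standard error is then too large precisely when MtCS works, which is the trial's own hypothesis.
- **Active vs sham.** Two group means and five slopes are estimated from about 26 patients. About 13 waitlist patients with the same covariates and outcome could help to estimate the slopes and the residual variance, but are left out.

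In a trial of 45 patients, a few points of power available without further recruitment are worth considering. The question is how many points, and under what assumptions.

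**Working it through.** **Inputs.** Two-sided alpha 0.05, 80% power, d = 1, 13 + 26 evaluable and 15 + 30 randomised (Sample size calculation); 2:1 allocation (Randomization); five covariates (Data analysis). Assumptions: the EMDR group splits evenly, giving 13/13/13; within-arm SD is 1 in every arm; slopes are common; covariates explain nothing (R2 = 0) unless stated. The active-sham difference m is also an assumption, so a range is shown.

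**The plan's own figure.** For a plain t-test at 13 + 26, the noncentrality is √(13 × 26 / 39) = 2.944 with 37 df, and power is 81.8%. At 12 + 24 it is 78.5%. The stated 13 + 26 reproduces.

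**Active vs sham.** Estimating q covariate slopes inflates the variance on average by 1 + q/(residual df − 1).

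- Planned model: 26 − 7 = 19 df; inflation 1 + 5/18 = 1.278; noncentrality √(6.5/1.278) = 2.255; power 57.2%.
- Three-arm model: 39 − 8 = 31 df; inflation 1 + 5/30 = 1.167; noncentrality √(6.5/1.167) = 2.360; power 62.8%.

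Simulation gives 57.8% and 62.9%. The difference in df alone (19 vs 31) accounts for only 1.8 points (67.7% vs 69.5%); the rest is slope estimation and chance covariate imbalance. With R2 = 0.25 the pair is 70% and 75%, and with R2 = 0.40 it is 79% and 84%. At m = 0.5 it is 19.1% and 21.0%.

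**EMDR vs waitlist.** With 26 EMDR patients split evenly and m = 1, merging the arms adds 26 × 0.5² = 6.5 to the residual sum of squares. Without covariates that is 6.5/37 = 0.176 on the residual variance, so the standard error is √1.176 = 1.084 times what it need be. At m = 0.5 the addition is 1.625/37 = 0.044, or about 2% on the standard error.

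Simulated power at mean EMDR effect d = 1, 13 per arm, five covariates:

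| Active-sham difference | Planned, arms merged | Three-arm contrast | Loss |
|---|---|---|---|
| 0 | 75.4% | 75.2% | none |
| 0.5 SD | 74.1% | 75.4% | 1.3 points |
| 0.8 SD | 71.8% | 75.2% | about 3.5 points |
| 1 SD | 69.8% | 75.4% | 5.6 points |

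**If all 45 are analysed** (15 per arm, with d = 1 for EMDR and m = 1): active vs sham 66.4% and 70.8%; EMDR 77.7% and 82.3%.

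**What the joint model risks for active vs sham.** If EMDR-arm SDs are 1.3 times the waitlist SD, the pooled variance is (12 × 1 + 24 × 1.69)/36 = 1.46 where 1.69 is needed. The standard error is then √(1.46/1.69) = 0.93 of its proper size, and the true error is about 6.4% to 6.9%, against about 5% for the EMDR-only model. If baseline pain has slope 1.0 in waitlist and 0.3 in the EMDR arms (assumed values), the gain shrinks to about 1 point (57.1% to 58.3%). An HC3 standard error in the joint model has about 54% power at m = 1, which is below the planned model.

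**The case against.** The strongest reply is that nothing here is an error. Both planned tests are unbiased and hold their error rate, each follows one stage of the randomisation, and the EMDR-only model needs no assumption about variance or slopes in untreated patients. That stands. Two-stage randomisation does not prevent a three-arm model, but it does make the plan's structure an ordinary choice.

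A reader might infer more than the protocol supports:

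- **That about 5 points are lost in each comparison regardless.** This needs a 1 SD active-sham difference. The only planning effect, d = 1, is stated for EMDR, so 5 points is the top of the range.
- **That MtCS always takes the larger loss.** With both effects at 1 SD and 13 per arm, EMDR loses slightly more (5.6 vs 5.1 points).
- **That the main test has the wrong size.** With a mean EMDR effect of zero and the arms 1 SD apart, the merged test rejects about 3.8% of the time. That requires one EMDR arm to be 0.5 SD worse than waitlist. If neither treatment works, size is nominal.
- **That a robust variance makes the joint model safe at no cost.** HC3 gives back more power than the joint model gains.

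The trial also calls itself exploratory, and MtCS is its secondary comparison, so the practical consequence is modest.

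**Conclusion.** The point holds as a matter of efficiency, not validity, and is an optional improvement.

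For the main comparison the case is clear. The planned model already shares slopes and variance between waitlist and EMDR, so separating active from sham adds no new assumption of that kind. It targets the same effect when the EMDR arms are equal in size. It recovers up to about 5 to 6 points if MtCS has a 1 SD effect, about 1 point at 0.5 SD, and costs almost nothing if MtCS has no effect.

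For active vs sham it is a trade-off: about 5 points at 1 SD and 2 at 0.5 SD, bought by borrowing variance and slopes from waitlist patients. Even then power stays at about 63% (13 per arm) to 71% (15 per arm) when covariates explain little.

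All of this rests on even arms, a common SD and common slopes. The size of any MtCS effect is an assumption throughout.

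**What to change.** In the Randomization and Data analysis sections, specify for the main comparison one linear model on all randomised patients, with arm as a three-level factor and the five planned covariates. Test the mean of the two EMDR arms minus waitlist. This costs one degree of freedom (31 instead of 32 at 39 patients).

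Active minus sham may be taken from the same model. If so, keep the planned EMDR-only model as the pre-specified check, rather than HC3. State the downside beside it: residual variance and slopes are shared with waitlist, true error could reach about 6.4% to 6.9% if EMDR-arm SDs are 1.3 times the waitlist SD, and the gain largely disappears if slopes differ.

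The change is one of wording and needs no extra patients or data. The Trial status section says the trial is to restart from the beginning, so it can be set down before any restarted data exist.

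### As written, the biased coin does not deliver 2:1 in expectation: about 25 EMDR and 20 waitlist patients should be expected, not the planned 30 and 15

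*Protocol article*

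**What the plan says.** The Randomization section of the protocol article describes two successive randomisations, first EMDR versus non-EMDR and then active versus sham MtCS within EMDR. It details only the first:

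- **Start:** "The first two patients will be randomly allocated to EMDR with *p* = 2/3".
- **Ratio step:** when a group holds at least two patients beyond the number needed "to maintain the ratio 2 EMDR / 1 control, the patient will be randomly assigned to the other group with" probability 0.6.
- **Balancing step, in all other cases:** compute the standardised pain difference with the new patient placed in each group in turn, then "randomly allocate the patient to the group associated to the smallest difference with *p* = 0.6".

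The second randomisation is not spelled out, "because the randomization to active-MtCS vs. sham-MtCS is identical".

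The Sample size calculation section relies on the 2:1 ratio. It requires 13 and 26 evaluable patients for d = 1 at two-sided 0.05 and 80% power and, allowing for 15% dropout, states: "we will aim to randomize 45 patients, i.e., 15 + 30".

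**The concern.** To hold 2:1, the chance of EMDR must average 2/3 over the patients. The article gives 2/3 only to the first two. From the third patient on, even the step meant to pull the trial back towards EMDR gives it 0.6, which is less than is needed merely to stay at 2:1. The balancing step ignores the ratio: it favours whichever group gives the smaller pain difference, so EMDR is chosen about half the time. The stated rule and the stated sizes therefore do not fit together, and nothing elsewhere in the article adds a 2:1 weight to the 0.6 coin.

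At stake are the group sizes the trial will report, the number of patients who wait, and the number available for active versus sham, which draws only on the EMDR group.

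**Working it through.** **Inputs.** From Randomization: 2/3 for patients 1 and 2, a trigger at an excess of two, and 0.6 in both later steps. From Sample size calculation: N = 45 as 15 + 30, 13 + 26 evaluable, d = 1, two-sided 0.05, 15% dropout. Assumed, because the article does not give them: the distribution of pain scores, and a 1:1 active/sham split.

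**1. The plan's own sample size.** Exact noncentral-t power at d = 1 is 78.5% for 12 + 24 and 81.8% for 13 + 26. So 13 + 26 is the smallest 2:1 design that reaches 80%. For dropout, 39 / 0.85 = 45.9 and 39 × 1.15 = 44.9, so 45 is reasonable. The sample size is reproduced.

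**2. Upper bound on EMDR enrolment, whatever the pain data.** From patient 3 on, P(EMDR) is 0.6 or 0.4. Hence

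E(EMDR) ≤ 2 × 2/3 + 43 × 0.6 = 1.33 + 25.8 = 27.1 of 45.

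This bound needs no simulation and already lies below 30.

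**3. Expected split.** The algorithm was simulated for 45 patients (6,000 runs per reading; pain normal with mean 7 and SD 1.5, limited to 4 to 10). The trigger wording allows three readings:

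| Excess counted | Mean EMDR : waitlist | SD | P(EMDR ≥ 30) |
|---|---|---|---|
| before the new patient | 25.4 : 19.6 | 2.5 | 3.0% |
| after the new patient | 25.2 : 19.8 | 2.5 | 2.6% |
| relative to the other group | 25.6 : 19.4 | 2.6 | 3.3% |

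The central 95% of trials runs from 20 to 30 EMDR patients. An exact recursion on the EMDR count (excess counted before the new patient), with the balancing step replaced by a fixed EMDR probability q, gives a mean of 25.4 at q = 0.5, and 24.8 to 26.9 as q runs from 0.4 to 0.6. The pain distribution therefore matters little; the 0.6 cap drives the result. A longer trial does not cure it: at q = 0.5 the EMDR share is 0.56 at 45 patients and 0.595 at 450, approaching 0.60 and not 0.667.

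**4. EMDR versus waitlist, power at d = 1.**

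| | Planned | Expected |
|---|---|---|
| Randomised | 15 + 30: 87.1% | 20 + 25: 90.3% |
| After 15% dropout | 13 + 26: 81.8% | 17 + 21: 84.7% |

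The more even split slightly raises power. Averaged over the simulated splits, power after dropout is 84%.

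**5. Active versus sham, power at d = 1, assuming 1:1.**

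| | Planned | Expected |
|---|---|---|
| Randomised | 15 v 15: 75.3% | 13 v 12: 66.7% |
| After 15% dropout | 13 v 13: 68.7% | 11 v 11: 60.7%, or 11 v 10: 58.4% |

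**The case against.** The strongest reply is that little of consequence follows. The only comparison the article sizes is EMDR versus non-EMDR, which Randomization names as the main analysis, and it loses no power. Allocation remains random and the total is unchanged. The comparison that shrinks is called secondary, has no stated power target, and would be under 80% at d = 1 even with the planned numbers. The article also describes the trial as exploratory. All of this stands, and it limits the severity. It does not remove the contradiction between the rule and the sizes.

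A reader might infer more than the documents support in four ways:

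- **That the trial is certain to end at 25 : 20 and can never return to 2:1.** These are expectations. A single trial can reach 30 or more EMDR patients by chance (about 3%), and about 18% to 25% of simulated trials, depending on how the trigger is read, end within two patients of 30.
- **That the main comparison is underpowered.** The fourth step of the working shows the reverse.
- **That the departure from 2:1 biases the comparison.** A different allocation ratio under a random rule does not.
- **That active and sham are to be allocated 2:1.** The article shortens the description for brevity, and the natural reading is the same procedure with its own target. The wording is ambiguous, and this is separate from the main point. It does affect the power figures: no active/sham ratio is stated, and on the literal 2:1 reading even the planned 26 evaluable patients would split about 17 v 9, with about 64% power at d = 1 instead of 69%.

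**Conclusion.** The point holds in expectation. The coin as published falls short of the ratio it is meant to maintain, and the 15 + 30 of the sample size section is not what it should be expected to produce. The bound of 27.1 rests on the text alone. The central figure of about 25 : 20 also depends on the balancing step favouring EMDR about half the time, and it is stable across the three readings of the trigger.

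The consequences are moderate: about five more patients on the waitlist than planned, and power for active versus sham falling from about 69% to about 58–61% (d = 1, after dropout, 1:1 assumed). The article should be corrected, but the defect does not threaten the validity of the main comparison.

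**What to change.** Do one of the following before the restart announced under Trial status.

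1. **Centre the coin on 2/3.** One workable set keeps 2/3 for the first two patients. In the balancing step, EMDR gets 0.80 when placing the patient there gives the smaller pain difference and 0.533 when the waitlist does; their average is (0.80 + 0.533) / 2 = 0.667. In the ratio step, EMDR gets 0.90 when the waitlist is over-full and 0.40 when EMDR is. Simulated, this gives a mean of about 30 EMDR patients, SD 1.4, with 97% of trials at 28 to 32. Other constants would also serve. Centring the balancing step alone, with the correction left at 0.6, reaches only about 28.5 : 16.5. The cost is a few constants in the randomisation code, one paragraph of text, and assignments that are somewhat easier to predict when the waitlist is over-full.
2. **Keep the coin and restate the sizes.** Give the expected numbers as about 20 + 25 randomised, with the likely range. This costs only text and preserves the power of the main comparison, but accepts the smaller active versus sham comparison.

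Neither option needs extra patients. As a separate wording correction, state the target ratio and the starting probability for the active/sham randomisation.
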